### Wearing of sunscreen

The secondary outcome will be children’s wearing of sunscreen during the school day. Currently no direct observation instruments to record the wearing of sunscreen exist. As a proxy measure of children wearing sunscreen, Grade 6 classes in control and intervention schools will be provided with one-litre containers of sunscreen for each class free of charge. Sunscreen will delivered to, and be collected from schools on the same day in order to ensure the period of use is the same in all schools; 50 days (10 school weeks) per interval. Each of the containers will their have branding removed but maintain their active ingredient information as required by the Therapeutic Goods Administration (TGA) [21]. A laminated instruction card will be attached to each bottle requesting classroom teachers to use the sunscreen as they normally would with their students.

The consumption of sunscreen from these containers will be recorded at the conclusion of the baseline, post-test and follow-up phases and will be replaced with full containers when they reach approximately 100 mL of sunscreen or less remaining.

In order to determine sunscreen consumption, 20 similar pump packs of sunscreen will be weighed to record an average starting weight for comparison. Consumption will then be analysed at the end of each data collection phase by comparing the net weight loss each pump pack of sunscreen issued to each school and the student number enrolled in Grade 6 classes who were issued the sunscreen.

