### Recruitment and study participants

To be eligible to participate in the study, schools must be government primary schools and be a current signatory to the SunSmart Program in the Greater Western Sydney Region, NSW, Australia (Approx 33.75 deg S, 150.70 deg E).

All eligible schools (n = 167) will be sent an initial email with an invitation to participate in the study. CCNSW and NSWDEC will also identify a short-list of schools that may be receptive to participating in the study (n = 40). Schools that respond to the initial email and the short-listed schools will be pooled and receive a follow up call in random order from the project researchers to ascertain whether they would like to participate in the study. The first twenty schools that demonstrate interest will then be recruited into the study.

Randomisation into intervention and control group will occur after baseline assessments. A simple computer algorithm will be used to randomly allocate schools to either control (n = 15) or the treatment (n = 5) conditions by an independent researcher not involved in the study. This method will ensure all schools have the same likelihood of allocation into one of the two study arms. Trained research assistants and project researchers will conduct all assessments and perform focus groups and interviews. All researchers will complete training sessions prior to assessment to maintain consistency and where possible, the same assessors will be used at baseline, post-test and follow-up. Figure 1 shows the flow of participants through the study.

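### Sunscreen use is computed from the average starting weight of 20 similar packs rather than each issued pack's own weight, which adds avoidable random error (minor)

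*Protocol article*

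**What the plan says.** All of the measurement rules are in the protocol article, Wearing of sunscreen.

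- **Role.** "The secondary outcome will be children’s wearing of sunscreen during the school day". The article calls the measure a proxy.
- **Issue.** Grade 6 classes in both arms "will be provided with one-litre containers of sunscreen for each class free of charge", for 50 school days per measurement interval.
- **Replacement.** Containers "will be replaced with full containers when they reach approximately 100 mL of sunscreen or less remaining", so a class may use more than one pack in a phase.
- **Starting weight.** "20 similar pump packs of sunscreen will be weighed to record an average starting weight for comparison".
- **Consumption.** It is analysed at the end of each phase by "comparing the net weight loss each pump pack of sunscreen issued to each school and the student number enrolled in Grade 6 classes".

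Under Recruitment and study participants, an independent researcher will "randomly allocate schools to either control (n = 15) or the treatment (n = 5) conditions". No section describes weighing an issued pack before it leaves for a school.

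**The concern.** The outcome is described as the net loss of each issued pack, but the only starting weight provided is a mean taken from other packs. A pack that starts heavier than that mean makes its class appear to have used less, and a lighter pack makes it appear to have used more. Averaging over 20 packs makes the mean precise. It does nothing about the scatter of single packs around the mean.

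What is at stake is the precision of the outcome the article names as secondary, in a trial with five intervention schools. A start weight not taken before issue cannot be recovered, and no later analysis can separate fill variation from use.

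**Working it through.** **Figures in the plan.** The article gives no expected use, SD or power for sunscreen, so there is no figure to reproduce. Its sample size section concerns headwear. Pack SD, use per class and between-class spread below are all assumptions. One millilitre is taken as about one gram.

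**Error in one pack.**
- Recorded use = mean of 20 packs − return weight.
- True use = own start weight − return weight.
- Error = mean of 20 packs − own start weight.

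With pack-to-pack SD s, the error has an independent part with SD s and a part shared by all packs with SD s/√20 = 0.22s. The total is s√(1 + 1/20) = 1.025s. Among classes using the same number of packs, the shared part largely cancels between arms.

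**Inflation of class-level variance in one phase.** With one pack per class and a between-class coefficient of variation of 0.3, the increase is s²/(0.3 × use)².

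| Use per class | Between-class SD | s = 10 g | s = 20 g | s = 30 g |
|---|---|---|---|---|
| 100 g | 30 g | 100/900 = 11% | 400/900 = 44% | 900/900 = 100% |
| 250 g | 75 g | 100/5,625 = 2% | 400/5,625 = 7% | 900/5,625 = 16% |
| 500 g | 150 g | 100/22,500 = 0.4% | 400/22,500 = 1.8% | 900/22,500 = 4% |
| 900 g | 270 g | 100/72,900 = 0.1% | 400/72,900 = 0.5% | 900/72,900 = 1.2% |

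Doubling the coefficient of variation to 0.6 divides every entry by four. At 100 g the increases become 3%, 11% and 25%.

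**Effect on the arm contrast.** Interval width follows the square root of variance. A 44% rise in variance is √1.44 = 1.20, or 20% in width. At 250 g the widths rise by about 1%, 3.5% and 8%.

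As a direct example, take s = 10 g, use 200 g with SD 100 g, one pack per school, and 5 versus 15 schools. Without the error, the SD of the arm difference is 100 × √(1/5 + 1/15) = 51.6 g. With it, the SD is √(100² + 10²) × √(1/5 + 1/15) = 51.9 g, a rise of about 0.5%. A simulation of the same case gave 51.5 and 51.8 g. The mean arm difference was 0.40 g without the error and 0.41 g with it (true value 0), so there was no sign of bias.

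**Change between phases.** If fresh packs are issued each phase, a change carries two independent errors, with SD s√2. With within-class correlation ρ between phases, the inflation of the change variance is s²/[SD²(1 − ρ)]. An assumed ρ of 0.5 doubles the percentages in the table. Writing x for a table entry, interval width then grows by √(1 + 2x) − 1, which is never more than x.

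**Replacement packs.** With k packs the independent error is s√k, but each replacement follows about 900 g of use. For fully used packs the relative error is s√k/(900k) = s/(900√k). With s = 20 g this is 2.2% for one pack and 1.6% for two. Just after a first replacement it is briefly 20√2/900 = 3.1%, which is still small.

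**The case against.** The strongest reply is that the point is too small to matter. The error is random with respect to arm. The large percentages need low use, a narrow spread between classes and pack variation of 2 to 3% of a roughly 1 kg pack, all at once, and the article supports none of these. The only level of use it points to is the replacement rule, which provides for classes that use about 900 mL in a phase. At that level the inflation is about 1% or less. The measure is also only a proxy for wearing sunscreen. All of this stands, and it is why the point is graded minor.

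It could also be said that "comparing the net weight loss each pump pack of sunscreen issued to each school" does not rule out individual weighing. That is true, but the article describes none, and individual start weights would leave the 20-pack average without a purpose.

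Three stronger readings are tempting, and the document does not support them:

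- **Bias in the arm comparison.** A reader might infer this, but nothing links a pack's fill to its school's allocation.
- **Replacements make heavy users the worst measured.** Absolute error does grow with √k, but relative error falls as full packs are used.
- **Negative consumption as a serious threat.** It would need a class using less than about one to two pack SDs over 50 days. Such a value would be near zero either way.

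**Conclusion.** The point holds as a minor matter of precision. The stated rule puts each pack's departure from the 20-pack mean into its class's value, and individual weighing would avoid this. It does not undermine the validity of the secondary outcome or of the arm contrast.

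The size is unknown. On the assumptions shown, the loss is negligible where a class uses 500 g or more or where use varies widely between classes. It becomes material only where use per class, or its spread, is small relative to pack variation. The main exception to this small estimate is an analysis of change in which classes are very stable between phases (ρ well above 0.5), where the loss would be larger than the single-phase figures suggest.

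**What to change.** Weigh and label every pump pack before issue, including replacements. For each class and phase, compute consumption as the sum over its packs of own start weight minus own return weight, divided by the number of Grade 6 students issued the sunscreen. Keep the 20-pack average only as a fallback for a pack whose start weight is lost, and flag those values.

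This removes the start-weight error apart from scale precision. The returned packs have to be weighed anyway, so the cost is a few minutes of weighing and record keeping per phase and one sentence in the methods. Schools carry no extra burden, and what is being estimated does not change.

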### Statistical methods

Statistical analysis of the primary and secondary outcomes will be conducted with linear mixed models using SPSS statistics version 20 (IBM SPSS Statistics, 2012) and alpha levels will be set at *p* > 0.05.

The models will be used to assess the impact of treatment (SunSmart Policy Intervention or Control), time (baseline, post-test and follow-up) and the group-by-time interaction, these three terms forming the base model. The models will be specified to adjust for the clustered nature of the data and will include all randomised participants in the analysis. Mixed models are robust to the biases of missing data and provide appropriate balance of Type 1 and Type 2 errors [22]. Mixed model analyses are consistent with the intention-to-treat principle, assuming the data are missing at random [23]. Sex, temperature/UV, time of day, type of period (recess or lunch) and conditions of target area (as previously outlined) will be included as covariates in the models.

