### Sample size calculation

Power calculations were conducted to determine the sample size and number of observations required to detect changes in the outcome of students wearing sun protective headwear in a cluster design. Calculations assumed baseline-posttest expected effect size gains of *d* = 0.4/r = 0.19 and were based on 80% power, with alpha levels set at p < 0.05. Using the standard deviation (SD) of change of SD = .5, it was calculated that the study required 50 observations within the intervention and control groups would provide adequate power to detect a between group difference of *d* = 0.4 across the school day.

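### Statistical methods prints the significance threshold with the inequality reversed (p > 0.05), contradicting the p < 0.05 of the sample size section: a minor error, but in the decision rule

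*Protocol article*

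**What the plan says.** The protocol article gives a significance level in two places.

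- **Sample size calculation.** The power calculation concerns students' use of sun protective headwear. Its error rates "were based on 80% power, with alpha levels set at p < 0.05".
- **Statistical methods.** The linear mixed models for the primary outcome (headwear) and the secondary outcome (sunscreen) are introduced with the statement that "alpha levels will be set at *p* > 0.05".

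No other part of the article gives a threshold, and no later sentence corrects either statement.

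**The concern.** The two statements use the same number with opposite signs. A test at level 0.05 declares significance when the p-value falls below 0.05, as the sample size section has it. The Statistical methods section has it the other way round.

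The location gives the slip some weight. A reader looking for the pre-specified rule goes to the analysis section, and for the sunscreen outcome there is nowhere else to look, because the power calculation deals only with headwear. A published protocol is the public record of what was fixed in advance. Its threshold should be correct where the analysis is described, without the reader having to infer it from the power paragraph.

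**Working it through.** **1. The two statements side by side**

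| Section | Scope | Threshold as printed |
|---|---|---|
| Sample size calculation | power for headwear | p < 0.05 |
| Statistical methods | primary and secondary outcome models | p > 0.05 |

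Both cannot be right. An extraction fault looks unlikely, because the sign in the sample size section came through intact and the sentence in Statistical methods is otherwise clean.

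**2. Which sign fits the article's own sample size**

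Inputs, all from Sample size calculation: 80% power, level 0.05, an effect of 0.4 ("Calculations assumed baseline-posttest expected effect size gains of *d* = 0.4/r = 0.19"), an SD of change of 0.5 ("Using the standard deviation (SD) of change of SD = .5"), and the result: "the study required 50 observations within the intervention and control groups would provide adequate power". Sidedness is not given, so I assume two-sided. Then z(0.975) + z(0.80) = 1.960 + 0.842 = 2.802 (unrounded 2.80158), and its square is 7.849.

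- Two groups, 0.4 read as a raw difference, SD 0.5: n per group = 2 × 0.5² × 7.849 / 0.4² = 24.5, rounded up to 25. The total is 2 × 25 = 50, which matches if 50 is a total.
- Change within one group, 0.4 read as a standardised effect: n = 7.849 / 0.4² = 49.06, rounded up to 50. This also matches.
- Two groups, 0.4 read as a standardised difference: n per group = 2 × 7.849 / 0.4² = 98.1, rounded up to 99. This does not match 50 per group.

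The article does not say which route was taken. Both routes that recover 50 use 0.05 as an upper cut-off on the p-value, that is, p < 0.05.

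**3. What the printed rule would do if applied literally**

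- Under a true null the p-value is uniform on 0 to 1, so the probability that p > 0.05 is 1 − 0.05 = 0.95. The intended rule gives 0.05.
- If the planned 80% power holds under the intended rule, the literal rule would declare that same true effect significant with probability 1 − 0.80 = 0.20.

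**4. Effect of the correction**

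Replacing > by < gives a level of 0.05, identical to the sample size section. The 50 observations were already derived at that level, so the number stays the same. The model terms and covariates do not depend on the sign.

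**The case against.** The strongest reply is that this is a self-evident misprint. An alpha level cannot sensibly be set at p > 0.05, the intended value is printed correctly elsewhere in the same article, and no competent analyst would apply the reversed rule. On that view the practical consequence for design, model and estimates is nil.

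Most of this stands. The intended level is clear, and the 95% figure describes only the literal wording. The reply does not remove the contradiction itself: the article chose to state its analysis threshold and stated it wrongly, so this is not a detail left to a statistical analysis plan that is not shown.

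Three stronger readings are tempting, and the document does not support them.

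- *That the trial would reach the wrong conclusion on every test, or that the threshold is fixed nowhere else.* The sample size section also gives the level, correctly, for the primary outcome, and that is enough to show what was meant.
- *That the unstated sidedness is part of the fault.* The article does not say whether tests are one- or two-sided, but a condensed article may leave that to the full protocol or analysis plan. It is also independent of the reversed sign.
- *That the sign error shows the trial to be underpowered.* With 50 independent observations per group and 0.4 read as a standardised difference, two-sided power is about 0.52. With 0.4 as a raw difference and SD 0.5 it is about 0.98. The result turns on how an ambiguous sample size paragraph is read and does not follow from the sign. Neither figure allows for clustering or for the allocation of 15 control and 5 intervention schools, so neither is this trial's power.

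**Conclusion.** The point holds as a minor internal contradiction. The threshold in Statistical methods is printed with the wrong inequality and disagrees with Sample size calculation. No calculation in the article is wrong because of it.

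Read literally, the type I error would be 0.95 in place of 0.05; this needs only that p-values are uniform under the null. In practice the effect on sample size, model and estimates is nil, provided the analysts use the level in the sample size section, which is almost certainly what was intended. The sign is worth correcting because of where it stands, in the decision rule for both the primary and the secondary outcome.

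**What to change.** In Statistical methods, change the threshold to p < 0.05, so that it matches Sample size calculation. Check that any full protocol or analysis plan carries the same sign. The cost is one symbol, by correction notice if the article is already in print. The sample size, the mixed models and the data collection are unchanged.

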### Outcomes

Evaluation of the SunSmart Policy Intervention will involve a variety of instruments to report on sun protection behaviours that occur in primary schools. Trained research assistants who will be blind to the control or intervention allocation of the schools will conduct all assessments. All sun protection behaviour practices will be measured at baseline, post-test (12 months), and follow-up (15 months).

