### Wearing of headwear and prevailing environmental conditions

The primary outcome will be children’s wearing of a sun protective headwear during break periods of the school day (i.e. recess and lunch). Currently no direct observation instruments to record sun-safe behaviours of children in school settings exist. However several direct observation tools of physical activity do exist, and one of these will be adapted to capture sun-safe behaviour data in children. The System for Observing Play and Recreation in Communities (SOPARC) is based on momentary time sampling techniques in which systematic and periodic scans of individuals and contextual factors within predetermined target areas are made [20]. iPad tablets (Apple Inc, USA) installed with the iSOPARC Application Version 1.75 (CIAFEL, Portugal: http://ciafel.fade.up.pt) will be used to provide an objective measure of the wearing of hats by children during recess and lunch.

During a scan each subject is electronically coded and identified by; sex (male or female), intensity of activity (Sedentary, Walking, or Very Active), and whether they are a Child, Teen, Adult or Senior. For this study, given all the subjects will be children, the third battery of coding (Child, Teen, Adult or Senior) will be changed to detect whether the student is Unprotected (no hat), Partially-Protected (wearing a baseball cap), Fully-Protected (wearing a 360 degree brim; broad-brimmed or bucket hat) or Fully-Protected (wearing a peak cap with back flap; legionnaire hat).

Separate scans are made for females and males, and simultaneous entries are also made for time of day, temperature, UV radiation level, area accessibility, area usability and presence of supervision. Each observation is conducted twice during the recess and lunch breaks for both females and males. This results in each school having 24 observations conducted at each data collection period (i.e. baseline, post-test and follow-up).

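### The base model leaves the arms free to differ at baseline and does not adjust for baseline hat use, which costs precision if a school's hat use is only weakly to moderately stable over time

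*Protocol article*

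**What the plan says.** Under Statistical methods, the protocol article specifies linear mixed models with treatment, "time (baseline, post-test and follow-up) and the group-by-time interaction, these three terms forming the base model". On adjustment it says: "Sex, temperature/UV, time of day, type of period (recess or lunch) and conditions of target area (as previously outlined) will be included as covariates". Baseline hat use is not in that list, and nothing in the article holds the two arms to a common baseline mean.

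Under Recruitment and study participants: "Randomisation into intervention and control group will occur after baseline assessments". Schools are allocated to "either control (n = 15) or the treatment (n = 5) conditions".

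The section Wearing of headwear and prevailing environmental conditions defines what is to be analysed: "The primary outcome will be children’s wearing of a sun protective headwear during break periods of the school day". The same section gives the amount of data: "This results in each school having 24 observations conducted at each data collection period". The sample size section works on the scale of change: "Calculations assumed baseline-posttest expected effect size gains of *d* = 0.4/r = 0.19".

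**The concern.** With time as a three-level factor, a treatment term and their full interaction, each arm has its own mean at each wave. The interaction at post-test is then the difference between arms in change from baseline, and it subtracts the observed baseline difference in full.

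Because allocation follows baseline, the expected baseline difference is zero. The efficient correction for an observed imbalance is to subtract it in proportion to rho. Full subtraction over-corrects whenever rho is below 1. With only five intervention schools, chance imbalances will be large and precision is scarce, while the baseline data needed for a better contrast are already being collected.

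**Working it through.** **Inputs.** From the article: 5 intervention and 15 control schools; three waves including baseline; 24 observations per school per wave; d = 0.4; SD of change 0.5; 80% power; alpha 0.05. Assumed: rho from 0.3 to 0.95; equal variance of school means at each wave; equal correlation between waves; two-sided tests. Results are in units of the SD of a school mean.

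**1. The plan's own figure.** With a difference of 0.4 and SD 0.5, the two-sample formula gives 2 × (1.96 + 0.84)² × 0.5² / 0.4² = 24.5, so 25 per arm and 50 in total. A one-sample change with d = 0.4 gives (1.96 + 0.84)² / 0.4² = 49.06, so again 50. Either way, the stated 50 fits a calculation on change with no baseline adjustment.

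**2. Planned contrast.** Variance = 2(1 − rho) × (1/5 + 1/15). Since 1/5 + 1/15 = 0.267, this is 0.373, 0.267 and 0.160 at rho 0.3, 0.5 and 0.7. Generalised least squares on all three waves with free arm means gives the same values.

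**3. Common or adjusted baseline, slope known.** Variance = (1 − rho²) × 0.267, that is 0.243, 0.200 and 0.136. The ratio to step 2 is (1 + rho)/2: 0.65, 0.75 and 0.85.

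**4. Slope estimated from 20 schools.** Estimating the slope inflates the variance by about 1 + 1/(20 − 4) = 1.0625. The table compares this with 20,000 simulated trials per rho, setting difference in change (18 df) against baseline as a covariate (17 df). Adjusted power is taken at the effect for which the planned contrast has 80% power. The last column is the minimum detectable difference at 80% power.

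| rho | Ratio, slope known | Ratio × 1.0625 | Ratio, simulated | Adjusted power | Detectable difference, planned → adjusted |
|---|---|---|---|---|---|
| 0.3 | 0.65 | 0.69 | 0.69 | 92% | 1.81 → 1.51 |
| 0.5 | 0.75 | 0.80 | 0.80 | 88% | 1.53 → 1.37 |
| 0.7 | 0.85 | 0.90 | 0.90 | 83% | 1.19 → 1.13 |
| 0.8 | 0.90 | 0.96 | 0.96 | 82% | 0.97 → 0.95 |
| 0.875 | 0.94 | 1.00 | 0.99 | 80% | 0.77 → 0.77 |
| 0.9 | 0.95 | 1.01 | 1.01 | 79% | 0.68 → 0.69 |
| 0.95 | 0.975 | 1.04 | 1.04 | 78% | 0.48 → 0.49 |

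At rho 0.5, 1/0.80 = 1.25, which is the information from about a quarter more schools.

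**5. Size of a chance imbalance.** The standard error of the baseline difference is √0.267 = 0.52. Given an imbalance of one standard error at rho 0.5, the difference in change is shifted by (1 − 0.5) × 0.52 = 0.26. Over all randomisations these shifts average to zero.

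**6. What the article implies about rho.** Two readings of the SD of change are possible.
- If the outcome SD is 1, then 2(1 − rho) = 0.25 and rho = 0.875.
- If the outcome is yes/no with SD 0.5, then 2 × 0.25 × (1 − rho) = 0.25 and rho = 0.5.

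The article states neither, and neither is clearly at school level. As an illustration, take 24 independent observations per wave and a stable school effect. Then rho = ICC / (ICC + (1 − ICC)/24), which is 0.56, 0.73 and 0.86 at ICC 0.05, 0.10 and 0.20. Applying (1 + rho)/2 × 1.0625 gives reductions of about 17%, 8% and 1%. School-by-time variation would lower rho and raise the gain.

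**The case against.** The planned model is a legitimate analysis. It agrees with a sample size calculation framed as change, and it contradicts nothing in the article. One reading of the article's SD of change puts rho at 0.875, where adjustment gains nothing. All of this stands, and it limits the point to a recommendation on efficiency.

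A reader might infer more in three ways. The first is that regression to the mean biases the result. It does not: the shift in step 5 is conditional on a chance imbalance, and the contrast is unbiased over randomisations. The second is that the saving is the textbook 35%, 25% and 15% at rho 0.3, 0.5 and 0.7, or a third more schools at 0.5. Those figures treat the slope as known, which 20 schools do not allow. The third is that some gain is assured. The article gives no rho, and above about 0.87 the gain vanishes or turns slightly negative.

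The objection does not remove the point. The article states the model terms and the covariates, so this is more than a detail left to a fuller plan. Nor does it support presuming a very high rho: post-test and follow-up come 12 and 15 months after baseline, each school mean rests on 24 observations, and no linkage of individual children is described.

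**Conclusion.** The point holds as one of efficiency. The stated model spends precision on estimating a baseline difference that randomisation has already made zero in expectation. At rho 0.3 to 0.7, adjustment would cut the variance by about 31% to 10% and raise power from 80% to between 92% and 83%. From about 0.87 upward there is nothing to gain, and at 0.9 to 0.95 the cost is 1% to 4% in variance and one to two points of power. These figures rest on an assumed rho, equal variances across waves and school-level means. The possible gain is clearly larger than the possible loss, so the change is worth making, but the validity of the planned analysis is not in question.

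**What to change.** Preferred: keep all three waves and constrain the arms to a common baseline mean. The model then has time, treatment-by-post-test and treatment-by-follow-up, with no treatment main effect and no treatment-by-baseline term. Both must go: deleting only the main effect while keeping the full interaction refits the same model.

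Alternative: model post-test and follow-up only, with the school's baseline value of the same primary headwear outcome as a covariate. Since no linkage of children is described, the baseline value should be at school level, or by school and sex or break period.

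Do the same for sunscreen, using baseline consumption per enrolled Grade 6 pupil; rho for that outcome may differ. Fix the choice before post-test data are seen.

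Cost: a sentence or two in the analysis section and no new schools or data. The covariate version uses one degree of freedom (18 to 17). The common-baseline version drops a mean parameter, but its correlation must also be estimated, so the small-sample figures are the safer guide for it too. Either version may lose slightly if rho proves very high.
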